##### Referrals to health system weight management resources

We will compare the number of WNP referrals to health system weight management resources to the number of referrals by PCPs of patients in the matched cohort.

##### Patients’ engagement with health system weight management resources

We will compare the rate of engagement in health system weight management resources among WNP patients as compared to patients in the matched cohort.

##### Prescriptions for anti-obesity medications

We will compare the number of WNP prescriptions for anti-obesity medications to the number of prescriptions by PCPs of patients in the matched cohort.

##### Patients’ use of anti-obesity medications

We will compare the number of refills for anti-obesity medications among WNP patients to patients in the matched cohort.

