### Participants WNP eligibility

Primary care patients with a body mass index (BMI) ≥ 30 kg/m^2^ and at least one weight-related chronic condition (eg, type 2 diabetes, hypertension, hyperlipidemia, non-alcoholic fatty liver disease, obstructive sleep apnea) may be referred by their PCP to the WNP. WNP exclusion criteria include primary care received at a location other than the pilot clinic site and pregnancy or breastfeeding. Patients may be scheduled for a WNP appointment regardless of insurance type. However, patients’ eligibility and out-of-pocket costs for obesity treatments may differ based on insurance status; this will be taken into consideration by the Weight Navigator when working with patients to develop personalized treatment plans.

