### Recruitment

Patients will be referred to the WNP by PCPs. All patients scheduled for a WNP appointment will be eligible for participation in a single-arm, 12-month pilot study. We anticipate that the Weight Navigator will see approximately 4 patients per 4-h clinic session once per week. Accounting for vacations, holidays, and canceled appointments, we estimate that the Weight Navigator will see approximately 150 patients during the first year of the program.

All patients scheduled for a WNP appointment will be eligible for participation in a single-arm, 12-month pilot research study. A research project manager will contact scheduled patients by telephone at least 5 days prior to their appointment date to invite them to participate in research and describe the study processes. Individuals who desire to participate in research will complete an online informed consent document and the baseline survey prior to the WNP appointment using the RedCap survey platform (REDCap, n.d.). Recruitment will continue until we reach our target of 30 participants.

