#### Clinical impact of the WNP

##### Change in weight

We will abstract weight and height data from the EHR for all WNP patients who complete a clinic visit within the first 12 months of clinical program operations. We will evaluate average weight change among WNP patients during the 12 months following their WNP appointment. We will also identify a contemporaneous cohort of patients with obesity matched by gender and approximate age (within 10 years) to WNP patients. The matched cohort will be selected from another Michigan Medicine primary care clinic located less than 1 mile from the pilot site clinic and serving a similar patient population. We will compare between-group weight change among WNP patients and the matched cohort. In addition to evaluating mean weight change, we will also evaluate achievement of ≥5% body weight loss.

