### Data analyses

#### Quantitative data analysis

Measures of central tendency (eg, proportions, means, standard deviations) will be used for all descriptive analyses. We will calculate mean 3-month and 6-month weight changes from baseline. We will also calculate the number of participants that achieve ≥5% body weight loss at 6 and 12 months. We will compare between-group changes (ie, all WNP participants versus WNP research participants and all WNP participants versus matched cohort) in weight using a difference-in-difference analytic approach. Among WNP research participants, we will also calculate mean weight change based on MPOTA-WM data. We will conduct all analyses using Stata 15.

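### Refills and program engagement are compared as levels with no baseline, so any imbalance in prior treatment between WNP patients and the matched cohort would read as a WNP effect

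*Protocol article*

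**What the plan says.** All places are in the protocol article.

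- **Refills** (Patients' use of anti-obesity medications) are defined in one sentence: "We will compare the number of refills for anti-obesity medications among WNP patients to patients in the matched cohort".
- **Engagement** (Patients' engagement with health system weight management resources) is also defined in one sentence: "We will compare the rate of engagement in health system weight management resources among WNP patients as compared to patients in the matched cohort".
- **Entry** (Participants WNP eligibility): patients need a BMI of at least 30 kg/m², "at least one weight-related chronic condition" and a PCP referral. The section continues: "WNP exclusion criteria include primary care received at a location other than the pilot clinic site and pregnancy or breastfeeding". Current drug treatment and current program enrollment are not listed.
- **Comparison cohort** (Clinical impact of the WNP, Change in weight): patients with obesity from a nearby clinic, "matched by gender and approximate age (within 10 years) to WNP patients".
- **Analysis** (Quantitative data analysis): between-group changes are compared "in weight using a difference-in-difference analytic approach". No method is named for refills or engagement.
- **Prescriptions** (Prescriptions for anti-obesity medications), for contrast: "We will compare the number of WNP prescriptions for anti-obesity medications to the number of prescriptions by PCPs of patients in the matched cohort". The referral outcome likewise counts referrals made by the WNP.

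**The concern.** Refills and engagement are both listed as clinical impact of the program, so a difference between groups will be read as something the WNP brought about. As defined, each also takes in treatment that was running before the WNP appointment. A patient who arrives on an anti-obesity drug and keeps refilling it adds to the refill count. A patient already in a long-running program adds to the engagement rate. Table 1 makes such carry-over realistic: one listed program lasts at least two years, and post-bariatric follow-up is offered for life.

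Prior users may be in the cohort too, so their presence alone does no harm. The harm comes from unequal proportions, and nothing stated makes the proportions equal. WNP patients want to lose weight, were referred by a PCP and have a weight-related condition. Cohort members are described only as having obesity and matching on gender and age. At stake is whether these two outcomes can separate treatment the WNP set in motion from treatment patients brought with them, before they inform the larger trial described under Future directions.

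**Working it through.** The article gives no figure to reproduce here. The check has two parts: reading the definitions against each other, and an illustration.

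**1. Baseline handling by outcome**

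| Outcome | What removes earlier treatment or baseline level |
|---|---|
| Weight | Difference-in-difference |
| Survey measures | Defined as change from baseline |
| Referrals, prescriptions | WNP side limited to those made by the WNP |
| Refills | Nothing stated |
| Engagement | Nothing stated |

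One consequence is that a drug started before referral and continued afterwards drops out of the WNP prescription count but stays in the WNP refill count.

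**2. Illustration with zero WNP effect**

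The only input from the article is the group size. Recruitment says "we estimate that the Weight Navigator will see approximately 150 patients during the first year of the program". Assumptions: one control per WNP patient (150 per group), 6 or 12 refills per prior user per year, the prior-use proportions shown, and no new starts in either group.

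Expected refills = 150 × proportion of prior users × refills per user-year. For 10% versus 3% at 6 a year: 150 × 0.10 × 6 = 90; 150 × 0.03 × 6 = 27; difference 63.

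The last column is the chance that a two-sided 5% test of any drug use shows a difference. It uses Φ{[|p₁ − p₂| − 1.96·√(2p̄(1 − p̄)/n)] / √[(p₁(1 − p₁) + p₂(1 − p₂))/n]}, with n = 150 and p̄ the mean of p₁ and p₂. For 10% versus 3%: (0.07 − 1.96 × 0.02847)/0.02818 = 0.504, so 69%. The article plans no such test; it serves only as a yardstick.

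| Prior use, WNP vs cohort | Refills at 6 a year | Difference | Refills at 12 a year | Difference | Chance of a significant any-use difference |
|---|---|---|---|---|---|
| 3% vs 3% | 27 vs 27 | 0 | 54 vs 54 | 0 | 5% (nominal) |
| 5% vs 2% | 45 vs 18 | +27 | 90 vs 36 | +54 | 29% |
| 10% vs 3% | 90 vs 27 | +63 | 180 vs 54 | +126 | 69% |
| 20% vs 5% | 180 vs 45 | +135 | 360 vs 90 | +270 | 98% |
| 3% vs 10% | 27 vs 90 | −63 | 54 vs 180 | −126 | 69% |

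The last row shows how an effect can be hidden. If the WNP truly added 63 refills, the observed difference at 6 a year would be −63 + 63 = 0.

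Engagement follows the same logic. With no new engagement, the difference in rates equals the difference in prior enrollment, for example 10% − 3% = 7 percentage points.

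**3. Effect of a look-back**

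Take 10% versus 3% with stable use of 6 refills in the year before and the year after. The change is 90 − 90 = 0 in the WNP group and 27 − 27 = 0 in the cohort, so the spurious difference disappears. Removal is incomplete for recent starters. A drug begun two months before the index date gives about 1 refill in the look-back and 6 afterwards, a change of +5 not due to the WNP. This is why continuing users should also be shown separately.

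**The case against.** The strongest reply is that this is a condensed article. The two outcomes get one sentence each, and a counting window or new-user rule could sit in a fuller document. The exclusion list is introduced in a way that need not be exhaustive, and naming no method for refills and engagement is not the same as stating an unadjusted one. This limits the certainty of the point. It does not remove it, because the article does fix both outcomes as between-group level comparisons while giving weight and the survey measures a baseline.

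Three stronger readings are tempting, and the documents do not support them.

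- **That the bias favours the WNP.** A reader might infer that motivated, referred patients are more often on treatment at entry. That is plausible but not shown. PCPs might equally refer patients who have no current treatment. The Background says most PCPs seldom prescribe these drugs, and Study setting reports that only a minority of surveyed PCPs use medical weight management (21.5%) or surgery (18.7%). Prior use could be low in both groups.
- **That these outcomes are the plan's only evidence of changed treatment.** Referrals and prescriptions are separate outcomes, tied to the WNP on the WNP side. If the Weight Navigator started nothing, they would show it.
- **That refills dispensed before the appointment are counted.** No window is given. The firm reading is narrower: later refills of a drug started earlier are not set apart.

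It is also fair to say that use of medication may properly include continuation, so making new starts the main comparison would change the question. These are secondary outcomes of a pilot whose primary outcomes are feasibility and acceptability.

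**Conclusion.** The point holds for refills and engagement only. As written, both are level comparisons between groups not balanced on prior treatment, and no stated step removes that treatment. Any imbalance passes directly into the result and may create, inflate or hide an apparent WNP effect.

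The size cannot be derived from the documents. Under the assumptions shown it runs from none (3% versus 3%) to 135–270 excess refills (20% versus 5%), and to 63–126 too few when the imbalance is reversed (3% versus 10%). The prior-use proportions, refill frequency and 1:1 matching are all assumed; only the figure of about 150 WNP patients comes from the article. The conclusion does not depend on the direction of the imbalance. Because the outcomes are secondary in a pilot, this is a worthwhile improvement and not a threat to the study's main aims.

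**What to change.** 1. Extract refills and engagement from the EHR for the 12 months before the WNP appointment, and for the 12 months before a matched index date in the cohort, with the same rules in both groups.
2. Define both outcomes over a stated period after the index date and make the main comparison the between-group difference in change from the look-back, in line with the weight analysis.
3. As a supporting analysis, report new starts (no use or engagement in the look-back) and continuing users separately, with the number of each per group.
4. Leave the entry criteria and the WNP referral and prescription outcomes as they are.

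The cost is a longer date range in the EHR extraction, two revised outcome definitions and slightly more analysis. The look-back does not remove confounding by motivation and referral: such patients may start more treatment without any program, so these comparisons should still be described as preliminary.

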##### Change in survey measures

Research program participants will be asked to complete surveys at baseline, 6 months, and 12 months; we will determine changes in measures at 6 and 12 months compared to baseline. Survey measures include motivation to lose weight (Kullgren, 2016), perceived competence to lose weight (Williams *et al*., 1998), social support (Sarason *et al.*, 1987), and eating behaviors (de Lauzon *et al.*, 2004). At baseline, we will ask participants to report sociodemographic characteristics.

### Feasibility, acceptability, and preliminary effectiveness of adding remote weight monitoring by text messaging to the WNP

#### MPOTA-WM uptake

Determined by the number of individuals who consent to research divided by the number of individuals who self-report at least 1 weight measure by text message.

#### MPOTA-WM engagement

Determined by the number of self-reported weights divided by the total number of possible reporting days.

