MPOTA-WM participants will be asked to self-weigh at least once per week and report their weight data via text message. Participants without access to a home scale will be provided with one by the study team. Participants will be asked to use the same scale throughout the duration of the study. Participants will self-select the day(s) of the week and time of the day to receive the following text message: ‘Hello, this is your Weight Navigation Program Research Team. What was your weight in pounds today? Reply STOP to opt out of receiving messages from our team’. The WNP team will receive inbox notifications based on the following parameters, which have been adapted from prior literature (Baer *et al*., 2020): (1) weight gain of ≥ 3 pounds at any point; (2) weight loss of varying thresholds (eg, 3%, 5%, and 10% body weight loss); (3) non-response to MPOTA for weight management messages for 14 days; and (4) participants’ ‘STOP’ responses, indicating that they are discontinuing their participation in the text messaging program. The research project manager will initiate tailored outreach; those losing weight, for example, will receive a supportive EHR portal message while those gaining weight will receive a phone call to discuss barriers to weight management, individuals’ preferences and needs, and other available weight management options, as detailed in the WNP encounter note. Communication will be documented in the EHR and patients’ primary care, WNP, and/or weight management subspecialty providers will be alerted, as appropriate.

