#### Change in weight

We will evaluate change in weight from baseline to 12 months of follow-up among MPOTA-WM users. To account for potential differences between clinic and home scales, the first weight entered by text message will serve as participants’ baseline weight for remote weight monitoring and this will be compared with follow-up MPOTA-WM data.

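### MPOTA-WM engagement is a per-day ratio, but the request is at least one weight a week on self-chosen prompt days, so a participant who exactly meets it can score anywhere from about 14% to 100%

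*Protocol article*

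**What the plan says.** The article's section on MPOTA-WM engagement consists of one formula: the "number of self-reported weights divided by the total number of possible reporting days". It does not say whether a possible reporting day is any calendar day or only a day on which a prompt was sent.

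The reporting schedule is in the Intervention section. Participants are "asked to self-weigh at least once per week and report their weight data via text message". On timing: "Participants will self-select the day(s) of the week and time of the day to receive the following text message". The request is therefore a weekly minimum, and the number of prompts a week is each participant's own choice. Participants can leave the texting programme by replying STOP. A separate rule notifies the team of "non-response to MPOTA for weight management messages for 14 days", but that rule does not enter the engagement formula.

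The article gives no target or threshold for engagement.

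**The concern.** The request is counted in weeks and the score in days, and the number of days may differ between participants by their own choice. A score built this way need not show whether participants did what they were asked, and equal scores need not mean equal behaviour.

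The feasibility of adding remote monitoring is one of the article's four outcome categories. Within it, uptake and engagement are the only two quantitative feasibility measures named. The Future directions section says the pilot data will be used to refine the programme before a larger trial. If the engagement figure mostly reflects how many prompts people chose, or how a reader takes an undefined denominator, it is a poor guide for that purpose.

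**Working it through.** **Inputs from the article**
- Score: self-reported weights divided by possible reporting days (MPOTA-WM engagement).
- Request: at least 1 weight a week (Intervention).
- Prompt days a week, *d*: chosen by the participant, so 1 to 7 (Intervention).
- Period: 12 months, taken as 52 weeks or 365 days. The section on change in weight for remote monitoring says "We will evaluate change in weight from baseline to 12 months of follow-up among MPOTA-WM users".
- Target number of research participants: 30 (Recruitment).

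The article states no engagement figure, so there is none to reproduce. With *r* reports a week, the score is *r* divided by the possible reporting days a week.

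**Reading A: every calendar day is a possible reporting day**
- One weight a week: 52/365 = 14.2%.
- Every prompt answered on *d* days: *d*/7, from 14% (*d* = 1) to 100% (*d* = 7).

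**Reading B: only self-chosen prompt days count**

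| Prompt days a week (*d*) | One weight a week (1/*d*) | Every prompt answered |
|---|---|---|
| 1 | 100% | 100% |
| 2 | 50% | 100% |
| 3 | 33% | 100% |
| 4 | 25% | 100% |
| 5 | 20% | 100% |
| 6 | 17% | 100% |
| 7 | 14% | 100% |

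- Ranking: three weights a week on daily prompts score 3/7 = 43%. One weight a week on a weekly prompt scores 1/1 = 100%. The participant who supplies three times the data ranks lower.
- Upper bound: weights are counted against days, so if the system accepts weights beyond the prompt, two weights a week with *d* = 1 score 2/1 = 200%.

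**Effect on a group summary (prompt choices assumed)**

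Suppose all 30 participants report exactly once a week. On Reading B the summary is 100% if all chose one prompt day and 14% if all chose seven. With 15 of each, the pooled ratio is 30/(15×1 + 15×7) = 30/120 = 25%, and the mean of individual scores is (15×1 + 15×1/7)/30 = 57%. Reporting behaviour is identical in every case.

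**Weeks after STOP**

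The formula does not say whether days after a STOP reply remain possible. Take a participant with one weekly prompt who answers every prompt for *w* weeks and then stops. The score is *w*/*w* = 100% if later weeks are dropped and *w*/52 if they are kept: 8% for *w* = 4 and 50% for *w* = 26 (both values of *w* are assumed).

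**Weekly coverage**

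Count the weeks with at least one weight and divide by follow-up weeks. Anyone who meets the request scores 52/52 = 100% whatever *d* is. The participant sending three weights every week also scores 100%, and the one who stops after four weeks scores 4/52 = 8%.

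**The case against.** The best defence is that a possible reporting day most naturally means a prompted day, because participants choose the days on which they are asked. The ratio is then a response-to-prompt rate. Someone who asks for seven prompts and answers three has answered 43% of them, and it is coherent to rank that below someone who answers all of theirs. This stands, and it is a reason to keep that rate as a secondary description. It does not make the rate a measure of the weekly request, nor comparable between people who set themselves different numbers of prompts.

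A second defence is that a full protocol may define the denominator, and that a condensed article may leave such details out. That holds for the choice between pooling and averaging: the article specifies neither, so it cannot be criticised for pooling. It does not cover the formula itself, which the article prints alongside a schedule that it does not match.

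A reader might also infer more than the documents support:
- *Choosing more prompts lowers the score.* On calendar days the number of prompts is not in the denominator, and answering more of them raises the score. On prompt days the score falls only if reports do not rise in proportion.
- *Full adherence scores 14%.* The request is a floor. The 14% belongs to someone who does exactly the minimum, on calendar days or with seven prompt days a week.
- *A successful programme would be declared a failure.* No target, progression rule, sample size or test depends on engagement, and lapses are flagged separately by the 14-day notification.

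**Conclusion.** The point holds as a mismatch between the measure and the request. A participant who exactly meets the request can score from about 14% to 100%, depending on how an undefined term is read and on how many prompt days that participant chose. On the prompt-day reading the order of two participants can run against the amount of data they supply (43% against 100%), and the score is not bounded by 100% if extra weights are accepted.

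The individual scores follow from the printed formula and schedule alone. The group example rests on an assumed mix of prompt choices, and the STOP example on assumed stopping times. They show that the score can move, not what the pilot will find.

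The consequence is limited to the interpretation of one feasibility outcome. Weight change, uptake and the comparison with the matched cohort are unaffected. The change is still worth making, because it replaces a figure that is hard to interpret with one that answers whether participants reported as asked.

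**What to change.** - Make the main engagement measure the proportion of follow-up weeks with at least one texted weight, computed for each participant and then summarised across participants.
- Keep weeks after STOP or silence in the denominator as not reported.
- Also show the result among participants who sent at least one weight, so that engagement stays distinct from uptake, which the article measures separately.
- Keep the response-to-prompt rate as a secondary description, defined as prompted days answered divided by prompted days. Counting days on both sides holds it at or below 100%.

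The cost is a few sentences in the plan and a little more analysis of the same message log. No new data are needed. The definition should be settled before the engagement data are examined.
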